## **4.2. Objectives**

### **Primary Objectives:**

- To evaluate the safety and tolerability of five different doses of VSVΔG-ZEBOV vaccine in three different age groups.

### **Secondary Objectives:**

- To evaluate the ZEBOV-specific antibody responses induced by VSVΔG-ZEBOV vaccine
- To evaluate VSV vaccine viremia and excretion after administration of VSVG-ZEBOV vaccine
- To relate status of pre-vaccination asymptomatic exposure to filoviruses of volunteers to ZEBOV-specific antibody responses

### **Exploratory objectives:**

- To evaluate immune response in the context of HLA allele expression
- To assay Ebola protein reactivity by Western Blot of any filovirus seropositives before vaccination
- To evaluate B-cell repertoire after vaccination
- To evaluate T-cell repertoire after vaccination
- To perform T-cell phenotyping after vaccination
- Obtain and preserve specimens to support assays to dissect the mechanism of the post-exposure protection observed in the NHP model
- To evaluate memory B- and T-cell responses up to 6 months after vaccination
- To isolate human antibodies in response to the vaccine

### 4.3. Endpoints

#### Primary Endpoints

The nature, frequency, and severity of adverse events (AEs) and/or serious adverse events (SAEs) associated with administration of BPSC1001 at 5 different doses measured as follow:

- Frequency and severity of local injection site reactogenicity signs and symptoms: pain, erythema, and induration until day 14 post vaccination (solicited local symptoms)
- Frequency and severity of systemic reactogenicity signs and symptoms until day 14 post vaccination (solicited general symptoms)
- Frequency of adverse events (AEs), severity and assessed relationship to study products until day 28 post vaccination (unsolicited AE)
- Detailed description of all serious adverse events (SAEs) until day 28 post vaccination
- Distribution of values of safety laboratory measures at baseline and at follow-up visits post-vaccination until day 28 post vaccination (reference ranges will be age appropriate)
- Number of participants with early discontinuation of vaccinations and reason for discontinuation until day 28 post vaccination

#### Secondary endpoints:

- Detailed description of all serious adverse events (SAEs) until study last visit (month 6)
- Concentration of ZEBOV envelope glycoprotein-specific binding antibody by ELISA
- Concentration of ZEBOV-specific neutralizing antibody at time points as considered in Table 3
- Concentration of rVSV in blood, urine, or saliva as detected by RT-PCR at time points as considered in Table 3

#### Exploratory endpoints:

Exploratory objective will be performed in sub samples of study participants. An experimental plan with detailed information will be specified in the course of the trial. However, blood will be collected and cells cryopreserved in all participants.

- To evaluate pre-vaccination of volunteers status on the ZEBOV-specific antibody responses

- Measurement of ZEBOV envelope glycoprotein-specific binding antibody by competition assays and Western blot analysis, including pre-vaccination positive samples
- Determination of HLA allele status at screening
- Determination of B-cell repertoire before and after vaccination (screening and day 28, 84, 180)
- To evaluate T-cell repertoire before and after vaccination (screening and day 28, 84, 180)

#### 4.4. Investigational Products

IDT-BIOLOGIKA GMBH manufactured the investigational product that will be administered via IM injection.

BPSC1001 vaccine is shipped by air carrier to the clinical site on dry ice to maintain the product at  $\leq -70^{\circ}\text{C}$ . Each shipment is accompanied by a Clinical Investigational Material Shipment Receipt Form and a Certificate of Analysis for product release testing. Upon receipt, at the clinical site, the product is unpacked by a designated person(s) and immediately transferred to  $\leq -70^{\circ}\text{C}$  storage.

##### BPSC1001 Dosage Form, Route of Administration and Use:

The vaccine is supplied individually packaged in sterile 1.0 mL vials. Each vial contains vaccine virus frozen in a mixture of USP water for injection, human serum albumin (25%, USP) and 10 mM Tris, pH 7.2. After thawing, the content of the vials is a clear liquid. The vaccine concentrations in the vials are formulated as:  $1 \times 10^8$  pfu/mL (stock). For dilution to  $3 \times 10^6$  and  $3 \times 10^5$  pfu/mL the vaccine can be prepared by mixing 0.32 mL of stock vaccine with 10 mL of normal saline (USP) or, vaccine at  $2 \times 10^7$  pfu/mL is prepared by mixing 1 mL of stock vaccine with 4 mL of normal saline (USP). One mL of vaccine is administered to the deltoid intramuscularly using a 3 cc syringe with a #25-gauge needle.

The lower doses of  $3 \times 10^3$  and  $3 \times 10^4$  will be diluted as per the pharmacy manual to be provided by the company.

Table 2: Study products characteristics

| Product Name                             |  | BPSC1001                                                                          |
|------------------------------------------|--|-----------------------------------------------------------------------------------|
| Dosage form                              |  | Liquid                                                                            |
| Unit dose/Injection volume i) |  | $1 \times 10^8$ pfu/mL (stock)                                                    |
| Route of administration                  |  | IM injection deltoid region                                                       |
| Physical description                     |  | Clear, colorless solution                                                         |
| Manufacturer                             |  | IDT-BIOLOGIKA GMBH                                                                |
| Lot number                               |  | 003 05013                                                                         |
| Product indication                       |  | Intended for human use in adults as a prophylactic measure against EBOV infection |

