| VSVΔG-ZEBOV vaccine                                       | VSVΔG-ZEBOV, a recombinant vesicular stomatitis virus (VSV) expressing the envelope glycoprotein of Ebola Virus Zaire                                                                                                                                                                                                                                                                                                                                                                                                                                                                                                                                     |
| Form                                                      | The vaccine is supplied individually packaged in sterile 1.0 mL vials. Each vial contains vaccine virus frozen in a mixture of USP water for injection, human serum albumin (25%, USP) and 10 mM Tris, pH 7.2. After thawing, the content of the vials is a clear liquid.                                                                                                                                                                                                                                                                                                                                                                                 |
| Route of Administration
Dose per administration | 
Intramuscular injection into the deltoid region of the upper extremity, using a 3mL syringe with a 1 to 1.5 inch #25-gauge sterile needle.
 
The vaccine concentrations in the vials are formulated as: <math>1 \times 10^8</math> pfu/ml (stock).
 
Cohort 1: <math>3 \times 10^5</math> pfu each dose (IM)
 
Cohort 2: <math>3 \times 10^6</math> pfu each dose (IM)
                                                                                                                                                                                                                                                              |

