## 4. Trial Design

### 4.1. Overview

LA-BPSC10001-01 is a Phase I, open-label, randomized, dose escalation trial. LA-BPSC10001-01 is designed to establish safety, tolerability and immunogenicity of three dose levels of VSVΔG-ZEBOV, an Ebola Virus Vaccine Candidate for the first time in sub-Saharan African populations. In LA-BPSC10001-01 trial, 201 volunteers will be randomized. The study will be conducted in Lambaréné, Gabon. There will be seven cohorts. Cohort 1 will be of participants receiving the dose  $3 \times 10^5$  pfu, cohort 2 will receive  $3 \times 10^6$  pfu of VSVΔG-ZEBOV and cohort 3  $2 \times 10^7$  pfu. Cohort 4 will be receiving the lowest dose of  $3 \times 10^3$  pfu, followed by cohort 5 which will receive  $3 \times 10^4$  pfu. Cohorts 6 and 7 will receive  $2 \times 10^7$  pfu. All doses will be administered intramuscularly. Vaccination of subjects in each cohort will proceed in a staggered fashion. Eligible adult volunteers will be randomized into the first 5 study cohorts. However, at the time of the submission of the study amendment 3, 60 eligible participants were already randomized and vaccinated in the cohort 1, 2 and 3 (20 into cohort 1, 39 into cohort 2 and one into cohort 3). Therefore, new randomization list will be generated according to the study requirements of having additional 61 vaccinees in the cohort 3, 20 in the cohort 4 and 20 in cohort 5.

On Day 1, the 1st volunteer of cohort 1 will be vaccinated, followed by the 2nd and 3rd volunteer on Day 3. If no safety concerns arise a group of 5 participants will be vaccinated on day 5. If the holding criteria have not been met and there are no safety concerns, the

next 5-10 participants will be vaccinated. Upon completion of visit 5 by the first 5-10 vaccinees of cohort 1 the DSMB' will do a review of safety data. Cohorts 2 and 3 will be run in parallel upon the go decision of DSMB after safety data review. Participants will be enrolled in Cohorts 3,4,5,6 and 7 and vaccinated in an identical manner to the Cohort 1 and 2. Children and adolescents will be enrolled and vaccinated into cohort 6 and 7 respectively only after the first 10 participants vaccinated in cohort 3 have reach D 28 follow-up. Following the first 10 participants, volunteers will be vaccinated in groups of 5-10 per day irrespective of the cohort. Vaccinees will be observed 30 min to one hour after vaccination and occurrence of any reaction will be carefully monitored.

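### Section 4.4 gives one dilution recipe for two concentrations that differ tenfold; followed as written, it gives cohort 1 about 10.3 times its labelled dose

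*Protocol*

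**What the plan says.** Section 4.4 (dosage form, route of administration and use) supplies the vaccine as a stock of 1×10^8 pfu/mL. One preparation is then given for two targets, 3×10^6 and 3×10^5 pfu/mL: "the vaccine can be prepared by mixing 0.32 mL of stock vaccine with 10 mL of normal saline (USP"). A separate preparation is given for 2×10^7 pfu/mL: "mixing 1 mL of stock vaccine with 4 mL of normal saline (USP"). On volume, the section states: "One mL of vaccine is administered to the deltoid intramuscularly using a 3 cc syringe". The 3×10^3 and 3×10^4 doses are referred to a pharmacy manual to come from the company. The 3×10^5 dose is not.

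The Synopsis (Groups, Sample Size, Dose per administration) and section 4.1 consistently assign 3×10^5 pfu to cohort 1 and 3×10^6 pfu to cohort 2. Section 4.1 also gives the numbers randomised and vaccinated when amendment 3 was submitted: "20 into cohort 1, 39 into cohort 2 and one into cohort 3". The first two match the planned sizes in the Synopsis, so both cohorts are complete.

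**The concern.** A single mixture has a single concentration, so the sentence cannot be right for both targets. With 1 mL injected, concentration in pfu/mL equals dose in pfu, and an error in one carries over in full to the other.

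Three things are at stake:

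- **The dose comparison.** Adults are randomised to dose, and the primary objective is safety and tolerability across five doses. The Synopsis and section 7 compare adverse event and seroconversion proportions between groups. If the recipe was followed for both cohorts, the contrast between them compares a dose with itself, and any dose-response uses a false value for cohort 1.
- **The escalation decision.** Under section 4.1, cohorts 2 and 3 proceed after the DSMB reviews the first cohort 1 safety data. That review would have concerned a dose ten times higher than stated.
- **Participant safety.** The 20 adults in cohort 1 would have missed the intended lower starting step.

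**Working it through.** **Inputs (section 4.4 unless stated)**

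- Stock concentration: 1×10^8 pfu/mL
- Recipe for 3×10^6 and 3×10^5 pfu/mL: 0.32 mL stock + 10 mL saline
- Recipe for 2×10^7 pfu/mL: 1 mL stock + 4 mL saline
- Injected volume: 1 mL
- Labelled doses (Synopsis, section 4.1): cohort 1, 3×10^5 pfu; cohort 2, 3×10^6 pfu

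**Formula:** concentration = stock concentration × stock volume / (stock volume + saline volume); dose = concentration × 1 mL.

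**1. The protocol's own figure for 2×10^7.** 10^8 × 1/(1 + 4) = 2.0×10^7 pfu/mL. This reproduces exactly, so the formula reads the section's recipes as intended.

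**2. The shared recipe.** 10^8 × 0.32/(0.32 + 10) = 10^8 × 0.32/10.32 = 3.10×10^6 pfu/mL.

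- Against cohort 2: 3.10×10^6 / 3×10^6 = 1.03, which agrees within rounding.
- Against cohort 1: 3.10×10^6 / 3×10^5 = 10.3, which does not agree.

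**3. Can another reading give 3×10^5?**

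| Reading | Result (pfu/mL) | Ratio to 3×10^5 | Supported by the text? |
|---|---|---|---|
| 0.32 mL stock made up to 10 mL in total | 10^8 × 0.32/10 = 3.2×10^6 | 10.7 | Arguable, but does not help |
| Same recipe applied twice | 3.10×10^6 × 0.32/10.32 = 9.6×10^4 | 0.32 | No |
| Further 1:10 dilution of the mix | 3.10×10^6 / 10 = 3.10×10^5 | 1.03 | No such step is stated |
| Stock of 1×10^7 pfu/mL | 10^7 × 0.32/10.32 = 3.10×10^5 | 1.03 | Contradicts the stated stock |

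Injecting 0.1 mL of the mix would also deliver 3.10×10^5 pfu, but it contradicts the stated 1 mL.

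**4. What a direct recipe would need.** For 3×10^5 pfu/mL with 10 mL saline, the stock volume is 10 × 3×10^5 / (10^8 − 3×10^5) = 0.030 mL, about one tenth of the 0.32 mL given.

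**5. Who is affected.** Cohort 1 has 20 of the 161 planned adults. The contrast between cohorts 1 and 2 involves 20 + 39 = 59.

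**The case against.** The strongest reply is that this is a dropped line, not an instruction to overdose. The mix is right for 3×10^6, and one further 1:10 dilution gives 3.10×10^5, so a lost serial-dilution step is the natural explanation. The wording is permissive (the vaccine *can* be prepared this way). Section 8.1 requires approved site-specific SOPs, which may hold the correct step. Every dose statement elsewhere assigns cohort 1 to 3×10^5. No remaining vaccination depends on the sentence: the adults still to be enrolled are in cohorts 3, 4 and 5, the minors receive 2×10^7, that recipe is correct, and the two lowest doses go to the manual. Even the hypothetical cohort 1 exposure of 3.1×10^6 is about the planned cohort 2 dose and roughly one sixth of 2×10^7 (3.1/20 = 0.155), so it lies within the range the trial tests.

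Much of this stands. A dropped step is likely, a wrong dose is not shown to have been given, and correcting the paragraph alters no planned dosing. It does not clear the text, however. For 3×10^5 the protocol gives its own instruction, offers no alternative and does not refer that dose to the manual. The SOPs are not shown. Because both cohorts are complete, a correction of the wording alone cannot settle what was injected; only the records can. An exposure within the tested range also limits the safety concern without rescuing the dose comparison or the escalation step.

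**Conclusion.** The concern holds. As written, section 4.4 contradicts the cohort 1 dose by a factor of 10.3 (10.7 if the mix is made up to 10 mL in total), while it is correct for cohort 2 to within 3% (7% on the same alternative reading: 3.2/3 = 1.07). The inconsistency is certain and rests only on the stated stock, volumes and injected volume.

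The consequences are conditional. If the recipe was used unchanged for cohort 1, there are no data at 3×10^5 pfu, the two cohorts form one dose group of 59, and the first safety review concerned about 3.1×10^6 pfu. If the pharmacy made a further 1:10 dilution, dosing was as labelled and only the text is wrong. The protocol alone cannot tell these apart. The point must be resolved before any analysis by dose, because the possible error is tenfold in the factor under study.

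**What to change.** 1. **Correct section 4.4.** Give each concentration its own preparation, consistent with the cohort doses and the pharmacy manual. For 3×10^5 pfu/mL, one option is 1 mL of the 3.1×10^6 mix plus 9 mL saline, which gives 3.10×10^5. The text must describe the method actually used.
2. **Check the records.** Before any analysis by dose, review the preparation and accountability records for the 59 adults in cohorts 1 and 2 and document the dose each received.
3. **Only if dose given and label differ:** analyse safety by dose received, relabel cohort 1 in all dose comparisons, and disclose the finding to the DSMB, whose go decision relied on the cohort 1 data.

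The cost is one corrected paragraph and a review of existing pharmacy records. The downside is that cohort 1 may have to be relabelled, which would leave the trial without a 3×10^5 pfu group.

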#### **4.5. Participation and study Duration**

The expected duration of individual enrolled subject participation will be approximately 6-8 or 12 to 14 months from the screening period. The date of signature of the informed consent form by the first volunteer is taken as the study start. The end of the trial is the date of the last visit of the last volunteer.

#### **4.6. Dose-adjustment Criteria**

##### **Safety Criteria for Dose Adjustment or Stopping Doses**

There will be no dose modifications.

##### **Individual Holding Rules**

As volunteers will receive a single vaccine dose, there will be no individual holding rules. Participants not meeting criteria for vaccination will be replaced by alternates.

##### **Holding Rules**

Participants will be followed a minimum of 60 minutes after vaccination. As such, immediate hypersensitivity reaction (in the 60 minutes following vaccination) will be assessed. All vaccinees will be monitored the day after injection in case of cytokine storm (in the 24 hours following vaccination). If any of the subjects has a vaccine related SAE, vaccinations will be held for the remainder of the study participants until a decision on vaccination resumption is reached. Vaccinations will resume upon agreement of the DSMB, the PI, the sponsor and VEBCON partner.

The following holding rules apply to each cohort of subjects. Solicited and unsolicited AEs and safety laboratory data will be recorded and tracked by the PI after immunization. The research monitor will review the AEs (local, clinical systemic, and laboratory systemic). If any holding rules are met, no further vaccination will be administered in any cohort until the investigators have conferred with the safety monitor and a full written report has been submitted to the Sponsor, the CERMEL SRC, the CERMEL IRB and the Gabonese NEC.

- One or more participants experience any SAE related to the study product (possible, probable or related), or
  - A suspected unexpected serious adverse drug reaction (SUSAR) occurs that is life-threatening or results in death.
- If any other observation occurs that in the opinion of the PI results in a recommendation to halt enrollment

After an holding rule is activated, a thorough review by the PI, safety monitor, and DSMB will occur. Vaccination of the subjects may resume only if the DSMB, the PI, and the sponsor agree it is safe to resume vaccinations and the following considerations are discussed.

- Relationship of the AE or SAE to the vaccine

- Relationship of the AE or SAE to the vaccine dose (eg, only associated with high dose group)
- If appropriate, additional screening or laboratory testing is provided to other subjects to identify subjects who may develop similar symptoms
- If any study related SAE is not listed on the current informed consent form (ICF), the PI will revise the ICF and volunteers will be asked to provide consent on the new ICF

The VEBCON partners will be notified if a holding rule is activated or released. If the clinical trial is halted and is unable to resume, a formal letter will be sent to the country specific regulatory authorities by the sponsor explaining the reasons for cessation of the study.

All vaccinated subjects will be followed for safety until resolution or stabilization (if determined to be chronic sequelae) of their AEs.

### **Study Termination Criteria**

The PI, sponsor's representative, the DSMB, and the appropriate regulatory authorities (national or international) may stop or suspend the use of this product at any time.

Significant numbers of arthritis cases have occurred among participant receiving the same vaccine, same batch number at high concentration from 1. 10^7 in Switzerland..

## **5. Selection and withdrawal of trial volunteers**

### **5.1. Volunteer recruitment**

Both health care workers and other community members, i.e. other adults living in the Lambarene area will be approached. Information on study recruitment is done by:

- Word-of-mouth, whereby health professionals working in the community and volunteers who have already been approached, mention the study to patients/family members/friends who go on to approach the study team. This is not solicited information sharing; merely an assumption that this will happen.
- Active approach by study team members, who will provide the Patient Information Sheet and discuss it with potential volunteers.
- Interviews and presentations (e.g. presentations at lectures or seminars).
- Advertising if requested

The investigators should be satisfied that there is no relationship or dependency that could coerce potentially vulnerable CERMEL or other health care workers to participate. In addition to the volunteers to be enrolled in the study, back-up volunteers who have been screened and are eligible to participate in the study will be identified. These volunteers will be available for enrolment at short notice should a planned volunteer withdraw consent or become ineligible immediately prior to enrolment. Backup volunteers will be asked to be available at short notice and may be asked to attend clinic on enrolment days.

## 5.2. Informed Consent

All volunteers need to sign and date the informed consent form before any study specific procedures are performed. The information sheet will be made available to the volunteer at least 24 hours prior to the screening visit. At the screening visit, the volunteer will be fully informed of all aspects of the trial, the potential risks and their obligations. The following general principles will be emphasised:

- Participation in the study is entirely voluntary
- Refusal to participate involves no penalty or loss of medical benefits
- The volunteer may withdraw from the study at any time, as described in section 5.5.
- The volunteer is free to ask questions at any time to allow him or her to understand the purpose of the study and the procedures involved
- There is no direct benefit from participating but travel to and from research site and time spent for participation will be compensated.

The aims of the study and all tests to be carried out will be explained. The volunteer will be given the opportunity to ask about details of the trial, and will then have time to consider whether or not to participate. The volunteer will be encouraged to discuss with their relatives. CERMEL has a research group working on the social components of clinical research. Before, during and after the trial, the study participants will be regularly reminded the purposes and procedures of the trial and clinical research in general. This approach showed to be more effective to ensure the understanding of the trial purposes by study participants.

Informed consent for children:

- Parents or guardians will be required to provide informed consent for minors (under the ages of 18), adhering to the same principles as above. This includes minors who are married.
- Assent will be sought from minors aged 11 to 17 years by engaging them in conversation about the study and ensuring they are not unwilling to participate. They will be asked to sign an assent document.
- Both assent and parental consent must be obtained for a minor aged 11 to 17 years to be enrolled in the study.
- As with recruitment for the adults, field workers who contact households are members of the community. They will seek to engage families, and will ensure minors and their parents/guardians will be given adequate time to discuss the study before being contacted again about consent.
- Contraceptive recommendations for minors will be primarily condoms; however oral contraception is also available. Parents will be made aware of contraceptive prescriptions for minors.
- Information on pregnancy and contraception will be provided to female minors who have reached menses, and to their parents in the assent and consent for parents/guardians. This will detail pregnancy testing, results and contraception.

